# Connectivity guided theta burst transcranial magnetic stimulation versus repetitive transcranial magnetic stimulation for treatment-resistant moderate to severe depression: study protocol for a randomised double-blind controlled trial (BRIGhTMIND)

**DOI:** 10.1136/bmjopen-2020-038430

**Published:** 2020-07-07

**Keywords:** depression & mood disorders, magnetic resonance imaging, health economics, adult psychiatry, clinical trials

## Abstract

**Introduction:**

The BRIGhTMIND study aims to determine the clinical effectiveness, cost-effectiveness and mechanism of action of connectivity guided intermittent theta burst stimulation (cgiTBS) versus standard repetitive transcranial magnetic stimulation (rTMS) in adults with moderate to severe treatment resistant depression.

**Methods and analysis:**

The study is a randomised double-blind controlled trial with 1:1 allocation to either 20 sessions of (1) cgiTBS or (2) neuronavigated rTMS not using connectivity guidance. A total of 368 eligible participants with a diagnosis of current unipolar major depressive disorder that is both treatment resistant (defined as scoring 2 or more on the Massachusetts General Hospital Staging Score) and moderate to severe (scoring >16 on the 17-item Hamilton Depression Rating Scale (HDRS-17)), will be recruited from primary and secondary care settings at four treatment centres in the UK. The primary outcome is depression response at 16 weeks (50% or greater reduction in HDRS-17 score from baseline). Secondary outcomes include assessments of self-rated depression, anxiety, psychosocial functioning, cognition and quality of life at 8, 16 and 26 weeks postrandomisation. Cost-effectiveness, patient acceptability, safety, mechanism of action and predictors of response will also be examined.

**Ethics and dissemination:**

Ethical approval was granted by East Midlands Leicester Central Research Ethics Committee (ref: 18/EM/0232) on 30 August 2018. The results of the study will be published in relevant peer-reviewed journals, and then through professional and public conferences and media. Further publications will explore patient experience, moderators and mediators of outcome and mechanism of action.

**Trial registration number:**

ISRCTN19674644

Strengths and limitations of this studyLarge multicentre randomised controlled trial of connectivity guided theta burst stimulation intermittent (TBS) versus standard repetitive transcranial magnetic stimulation (rTMS).Carefully characterised population of patients with treatment-resistant moderate to severe unipolar major depression with broad inclusion and exclusion criteria to enhance generalisability to clinical care.Explores efficacy, sustainability of treatment response, acceptability, cost-effectiveness cognitive function, mechanism of action using MRI and spectroscopy, and clinical and MRI predictors of response in the same sample.Unable to completely blind sound and sensation of the treatments being tested.Both nature of magnetic stimulation (TBS vs rTMS) and stimulation site identification vary between treatment arms.

## Introduction

The lifetime prevalence of major depressive disorder (MDD) is approximately 13% of the general population,^1^ and it is the most disabling health condition in terms of years lived with disability.^2^ Antidepressants and psychotherapies are effective in treating MDD. However, at least 33% of patients in specialist care,^3^ and 22% in general primary care,^4^ fail to respond to adequate trials of at least two antidepressants. Therefore, it is essential to find alternative treatments for such ‘treatment-resistant depression’ (TRD).

Neuromodulation techniques that attempt to directly modulate the function of targeted brain regions, such as electroconvulsive therapy (ECT),^5^ and repetitive transcranial magnetic stimulation (rTMS),^6^ can be effective treatments for MDD. rTMS uses powerful magnetic pulses that can be focused usually on the left dorsolateral prefrontal cortex (DLPFC) to produce changes in brain activity if it is given as a course of treatments. Unlike ECT, rTMS does not require anaesthesia nor produce potential cognitive deficits, and is cost-effective in TRD compared with current standard care.^7^

A recent meta-analysis in TRD demonstrated the acute effectiveness of rTMS when compared with sham TMS, showing significant reductions in depression symptoms, and increases in response and remission and response rates, after treatment.^6^ However, the beneficial effects of rTMS on mood in TRD may be relatively short, lasting only 1–3 months.^6 8^

Theta burst stimulation (TBS) is an alternative patterned form of TMS, which employs high frequency stimulation, with each treatment administration requiring less time. Unlike rTMS, TBS uses bursts of magnetic pulses that mimic endogenous theta rhythms and it is associated with cortical long-term potentiation that may induce plasticity in more distal brain areas, such as the hippocampus, potentially leading to a higher proportion of responders and a longer duration of effect in TRD.^9^ A meta-analysis of five randomised controlled trials (RCTs) in 221 patients with MDD,^10^ found unilateral intermittent TBS (iTBS) applied to the left DLPFC and consecutive iTBS applied to the left DLPFC and then continuous TBS applied to the right DLPFC to be robustly effective versus sham TBS on depression symptoms and response. One RCT demonstrating 83% of TRD patients given unilateral iTBS maintained their response at 14 weeks unlike sham and bilateral TBS.^11^ A large RCT of 414 TRD patients comparing iTBS versus rTMS to the left DLPFC showed a non-inferior reduction in depression symptoms after 4–6 weeks of treatment and at 1, 4 and 12 weeks after treatment.^12^ Thus, TBS requires a shorter duration of administration than rTMS without compromising clinical effectiveness. Further studies are required to maximise efficacy and durability of effect of TBS, identify its mechanisms of action and predictors of response.

Brain connectivity changes as detected by task-free, resting state functional MRI (rsfMRI) may individualise neurostimulation therapy of MDD,^13^ with the insula suggested as a target for neuromodulation.^14^ In depression, an altered network communication exists within and between affective, cognitive control and default mode networks,^15–18^ with a disruption of the reciprocal loop between the DLPFC and insula extending to the sensory regions.^16^ In addition, hypometabolism at the right anterior insula (rAI) predicts remission with cognitive–behavioural therapy and similarly, hypermetabolism at the rAI predicts remission with antidepressant treatment in patients with MDD.^19^ One biotype of MDD, characterised by strong connectivity between the insula and other regions of the brain, was related to partial treatment response to rTMS of at least 25% improvement on depression symptoms in 82.5% participants.^20^

Therefore, in a small pilot study of 27 TRD patients,^21^ individualised left DLPFC targets were determined using Granger causality analysis (GCA) to provide a measure of effective functional connectivity (eFC) seeded from the rAI. Of the 18 participants who completed all follow-up in the two treatment arms (connectivity guided rTMS (cgrTMS) and cgiTBS) higher response rates were found at 3-month follow-up favouring cgiTBS (89%) over cgrTMS (44%), indicating the potential for longer lasting efficacy of cgiTBS.

In addition, rsfMRI and MR spectroscopy (MRS) may advance neuromodulation therapy through mechanistic evaluation of effects and response predictions. iTBS may dampen fronto-insular eFC in responders with TRD.^21^ Left DLPFC gamma-aminobutyric acid (GABA) levels are increased significantly in rTMS responders versus non-responders.^22^ In addition, DLPFC targeted TMS normalises dysfunctional fronto-limbic networks in TRD, with decreased hyperconnectivity between the subgenual anterior cingulate cortex (ACC), ventromedial and dorsomedial prefrontal cortex and DLPFC.^23^ iTBS may induce widespread and longer-term network change but precise anatomical localisation of the target circuitry may be required for maximal efficacy of iTBS to normalise dysfunctional fronto-limbic circuitry. Such changes may increase the proportion of people with TRD who obtain a sustained response compared with neuronavigated rTMS. Thus, this multicentre RCT will examine the clinical and cost-effectiveness of cgiTBS in comparison with neuronavigated rTMS, in treatment-resistant moderate to severe MDD.

## Methods and analysis

### Study design

The study is a multicentre parallel group, double-blind, randomised, controlled trial of the efficacy of cgiTBS versus neuronavigated rTMS without connectivity guidance, in patients with a primary diagnosis of moderate to severe MDD, which is treatment resistant in their current episode (TRD). The study will be carried out at four sites across UK National Health Services (NHS): Nottinghamshire Healthcare Foundation NHS Trust, Northamptonshire Healthcare NHS Foundation Trust, Cumbria, Northumberland, Tyne and Wear NHS Foundation Trust and Camden and Islington NHS Foundation Trust. The study flow chart (figure 1) provides an overview of the study design and procedures.

**Figure 1 F1:**
[figure not shown]
Study flow chart. cgiTBS, connectivity guided intermittent theta burst stimulation; rTMS, repetitive transcranial magnetic stimulation; TRD, treatment-resistant depression.

### Study population and recruitment

A total of 368 participants will be recruited in total (184 per treatment arm). Recruitment of the first patient started 22 January 2019 but was suspended on 23 April 2020 because of the COVID-19 pandemic lockdown. The study is due to complete on 30 September 2021. Table 1 shows the detailed inclusion/exclusion criteria. Participant identification will occur through primary and secondary care NHS settings across the four sites.

**Table 1 T1:** Inclusion and exclusion criteria

Inclusion criteria	Exclusion criteria
Adults >18 years Diagnosis of current MDD (defined according to the DSM-5), that is, treatment-resistant defined as scoring 2 or more on the Massachusetts General Hospital Treatment Resistant Depression staging score (online supplementary appendix 1). Have a 17-Item Hamilton Depression Rating Scale score of 16 or more (moderate to severe depression). Capacity to provide informed consent before any trial related activities.	History of bipolar disorder (due to risk of mania) or depression secondary to other mental disorder. Neurological conditions, for example, brain neoplasm, cerebrovascular events, epilepsy, neurodegenerative disorders and prior brain surgery. Standard contraindications to MRI, that is, irremovable metal objects in and around body, for example, cardiac pacemaker, implanted medication pump, and pregnancy (any doubt resolved by pregnancy test, women of childbearing age taking precautions against pregnancy). This will include other potential complicated factors such as red tattoos which consist of iron on the head, neck and back and claustrophobia (we offer mock scanner testing and training in some sites). Major unstable medical illness requiring further investigation or treatment. Change in prescribed medication 2 weeks before baseline assessment. Prescription of lamotrigine, gabapentin, pregabalin in the 2 weeks prior to baseline assessment but may be used before then. Daily prescription of benzodiazepine above 5 mg diazepam equivalents, zopiclone above 7.5 mg, zolpidem above 10 mg or Zaleplon above 10 mg. These drugs should not be used intermittently in the 2 weeks before baseline assessment but may be used before then. Current substance abuse or dependence (defined by DSM-5 criteria). Prior TMS treatment. At risk of suicidality. Potential complicated factors relating to the TMS treatment, that is, hairstyles which would impair magnetic transmission and piercings. (Participants would only be excluded if they chose to not make the changes required to ensure effective treatment.) Involved with any other clinical trial at the time of consent or 6 months prior. Unable to read or understand English.

DSM-5, Diagnostic and Statistical Manual of Mental Disorders, Fifth Edition; MDD, major depressive disorder; TMS, transcranial magnetic stimulation.

10.1136/bmjopen-2020-038430.supp1Supplementary data

### Interventions

For all treatments, a 70 mm figure-of-eight coil (E-z Cool coil) and a Magstim Horizon Performance Stimulator with StimGuide Navigated TMS Package (Magstim Company, Whitland, UK) will be used. Participants in both treatment arms will receive neuronavigation-guided single coil stimulation for 20 TMS sessions delivered over 4–6 weeks. A total of 3000 pulses will be delivered in each rTMS or cgiTBS session. Each treatment session, irrespective of treatment arm, is designed to last approximately 37.5 min in total for the purposes of blinding the participants and assessors of outcome. There must not be a gap of more than 4 days between treatments in the course of 20. Medication will be unchanged over 16 weeks follow-up unless there is clinical risk of harm.

Individuals assigned to cgiTBS will receive bursts of three pulses (80% motor threshold) at 50 Hz applied at a frequency of 5 Hz (ie, every 200 ms) for 40 s duration over a site determined from the assessment of maximal strength of effective connectivity between the rAI and the left DLPFC from fMRI and structural MRI. Neuronavigation computes the nearest location for TBS stimulus on the scalp from an individualised head model based on structural MRI and three fiducial points, the nasion, left preauricular and right preauricular sites. If this site causes discomfort to the participant, it is moved by 1 cm in any direction until there is no discomfort. The pulses are repeated for a total of 5 runs with 5 min rest intervals between runs.

Individuals assigned to rTMS will follow the standard US Food and Drug Administration approved protocol. The site of stimulation will be determined using structural and fMRI utilising neuronavigation to compute the F3 electrode site over the left DLPFC for TMS stimulation from the same head model and three fiducial points. Stimulation is at 120% motor threshold with 75×4 s trains of 10 Hz interspersed by 26 s intertrain intervals.

### Primary clinical objective

Our primary hypothesis is that cgiTBS is more efficacious at 16 weeks than standard rTMS in patients with TRD as assessed by the proportion of patients who show a response (50% reduction in depression symptoms from baseline on the 17-item Hamilton Depression Rating Scale (HDRS-17)).

### Secondary clinical objectives

To explore secondary efficacy outcomes of the mean change in HDRS-17 scores between the two treatment arms and the proportion of patients meeting criteria for remission (HDRS-17 score ≤7) at 16 weeks.To explore secondary clinical outcomes of importance to patients and clinicians namely cognition, anxiety, social function and quality of life.To examine cost-effectiveness of cgiTBS versus rTMS in a UK NHS population.To examine the patient acceptability and patient experience of cgiTBS and rTMS.

### Mechanistic objectives

To investigate the neural mechanism of efficacy in cgiTBS and rTMS.To develop response prediction models from brain biotypes and clinical features.

Protocols for the study will be published separately describing the mechanistic objectives and localisation of sites of stimulation in greater detail.

### Study schedule

Trained researchers under the supervision of clinically trained investigators will obtain informed consent and undertake all assessments. A prescreening questionnaire will be used to telephone screen interested participants first, with potentially eligible participants invited to attend a baseline assessment. Written informed consent will be obtained and study eligibility determined at the baseline assessment.

Information on sociodemographics, medical and psychiatric history including a detailed assessment of treatment resistance will be obtained from case files and primary care notes. Diagnosis will be assessed by the Structured Clinical Interview^24^ for the Diagnostic and Statistical Manual of Mental Disorders, Fifth Edition (DSM-5).^25^

Treatment resistance will be measured by the Massachusetts General Hospital (MGH) TRD staging score (adapted for new treatment options—see online supplementary material appendix 1 and table 1).^26^

Depression severity and the primary outcome measure will be assessed using the GRID version of HDRS-17.^27^ The HDRS-17 and secondary outcome measures will be assessed in eligible patients at baseline, 8, 16 and 26 weeks postrandomisation (table 2). The primary outcome measure is a binary variable of responder or non-responder at 16 weeks. Individuals observed to have a 50% drop or greater in HDRS-17 from baseline to 16 weeks are defined as responders. In contrast, individuals with <50% reduction or a null value are classified as non-responders. The Childhood Trauma Questionnaire^28^ will be assessed at baseline as a moderator of treatment response at 16 weeks.

**Table 2 T2:** Study schedule and assessments

Outcome measures	Baseline assessment (consent to the study)	Baseline MRI scan	Treatment Monday–Friday for 4–6 weeks	8 weeks follow-up assessment	16 weeks follow-up assessment	16 weeks MRI scan	26 weeks follow-up assessment
Visit window		Within 14 days of Baseline Assessment	+14 days of MRI Scan	±1 week from Randomisation	±1 week from Randomisation	Within 14 days of 16 week Follow-up Assessment	±1 week from randomisation
HDRS-17	✓		✓Only if baseline assessment exceeds 4 weeks	✓	✓		✓
MGH	✓		✓ Only if Baseline assessment exceeds 4 weeks				
BDI-II	✓			✓	✓		✓
PHQ-9	✓			✓	✓		✓
WSAS	✓			✓	✓		✓
GAD7	✓			✓	✓		✓
EQ-5D-5L	✓			✓	✓		✓
THINC-it	✓			✓	✓		✓
SCID-5	✓						
CTQ	✓						
QIDS-SR	✓			✓	✓		✓
Client Resource Questionnaire	✓				✓		✓
Patient Acceptability			✓	✓	✓		✓
Side effects checklist (adverse events)			✓	✓			
fMRI		✓				✓	
MRI		✓				✓	
rsfMRI		✓				✓	
MRS		✓				✓	
Diffusion-weighted imaging		✓				✓	

BDI-II, Beck Depression Inventory-II; CTQ, Childhood Trauma Questionnaire; EQ-5D-5L, EuroQoL-five-Dimensions-5-Level; GAD-7, Generalised Anxiety Disorder-7; HDRS-17, Hamilton Depression Rating Scale-17; MGH, Massachusetts General Hospital; MRS, MR spectroscopy; QIDS-SR, Quick Inventory of Depressive Symptomatology; rsfMRI, resting state functional MRI; SCID-5, Structured Clinical Interview-5; THINC-it, THINC-Integrated Tool; WSAS, Work and Social Adjustment Scale.

Secondary outcome measures are the Beck Depression Inventory-II,^29^ Patient Health Questionnaire,^30^ Generalised Anxiety Disorder Assessment,^31^ Work and Social Adjustment Scale,^32^ EuroQol-five-dimensions-5-level,^33^ and cognitive functioning as measured by the THINC-Integrated Tool (THINC-it) (THINC-it Task Force, http://thinc.progress.im/en). Quick Inventory of Depressive Symptomatology^34^ is completed for a mechanism study (see online supplementary material appendix 2).

In addition, a purposely designed patient proforma will be used to collect patient NHS service utilisation information at the 16 and 26 weeks follow-up time points. This will cover relevant items listed in the Client Service Receipt Inventory,^35^ and tailor the resources items measured following good practice approaches used by the health economics database of instruments for resource use measurement group to estimate costs. Patient acceptability will be measured on a 1–5 scale from unacceptable to acceptable and patient experience of overall improvement will be assessed using the Patient Global Impression of Change (1–5 scale much worse to much better)^36^ after each TMS session and at each follow-up time point. A side effect checklist will be completed after each TMS session and 8 weeks follow-up assessment. We will note any changes in medication or other forms of treatment.

Participants will undergo baseline structural MRI, rsfMRI, diffusion weighted imaging scans to assess structural connections between relevant brain regions, and MRS scans (not in London where only fMRI and structural MRI scans will be performed). Treatment target identification will be analysed centrally in Nottingham and communicated to treatment sites. Using GCA of fMRI scans in each subject, coordinates for the stimulation target within the left DLPFC that shows maximal effective connectivity with the rAI will be identified. For the MRS scans, voxels will be placed in the DLPFC and ACC, using a similar method to prior work with the MEGA-PRESS sequence for GABA-edited MRS.^22^ The MRI scans are repeated at 16 weeks to assess FC, effective connectivity and GABA.

### Randomisation

Randomisation will take place immediately prior to the start of the first treatment session, with participants randomised to either rTMS or cgiTBS treatments. Randomisation will be conducted via a web-based randomisation system (Sealed Envelope, www.sealedevelope.com) by a named TMS nurse practitioner and healthcare assistant delivering TMS at each centre who will remain un-blinded. Participants will be randomly assigned in a 1:1 ratio into the rTMS and cgiTBS arms using blocks of varying size. Randomisation will be stratified by centre and minimised on severity of depression at baseline and degree of treatment resistance. Baseline depression will be measured by HDRS-17 score and classified as moderate (16-23) or severe (≥24).^37^ Treatment resistance will be measured by the MGH TRD staging score and, based on distributions of treatment resistance in the Antiglucocorticoid augmentation of anti-Depressants in Depression (ADD) study,^38^ degree of treatment resistance will be classified as low (2–3.5), medium (4-6) and high (≥6.5).

### Statistical analyses

#### Efficacy analysis

The primary analysis will test the null hypothesis that treatment with cgiTBS does not increase response rate as measured by HDRS-17 compared with rTMS at 16 weeks on an intent to treat population with any missing response data at 16 weeks being imputed as no response having been achieved. Response at 16 weeks was selected as the primary outcome because of the much larger response rate with cgiTBS than rTMS in our pilot study.^21^ A logistic regression will be fitted for the outcome of response with treatment arm, centre, baseline HDRS-17 score and MGH TRD score.

As a secondary analysis a logistic regression model will be repeated in completers (those with 10 or more rTMS or cgiTBS treatments, assessed at baseline and 16 weeks) and a per-protocol analysis. Secondary outcomes are the and proportion of responders and remitters at 8, 16 and 26 weeks, and sustained responders at both 16 and 26 weeks will be compared between groups using logistic regression adjusted for treatment centre, baseline HDRS-17 score and MGH TRD score (5% significance). All outcomes are shown in table 3. Repeated measure linear models will be used for continuous outcomes. Patient acceptability (5-point scale) and safety of both cgiTBS and rTMS (side-effects checklist) will be reported descriptively.

**Table 3 T3:** Study efficacy outcome measures

Outcomes	Measure	Time points
Primary Outcome	17-Item Hamilton Depression Rating Scale (HDRS-17)	Response at 16 weeks (defined as by a 50% or greater reduction in HDRS-17 score from baseline)
Secondary Outcomes	HDRS-17	Mean change in HDRS-17 score compared with baseline at 8, 16 and 26 weeks Response (as defined above) at 8 weeks and at 26 weeks Sustained response at 16 and 26 weeks (defined as a continuing response as defined above following a response at the previous time point) Remitters at 8, 16 and 26 weeks (defined as a score of 7 or less on the HDRS-17)
	Beck Depression Inventory-II	At 8, 16 and 26 weeks
	Patient Health Questionnaire Quick Inventory of Depressive Symptomatology	At 8, 16 and 26 weeks At 8, 16 and 26 weeks
	Generalised Anxiety Disorder Assessment	At 8, 16 and 26 weeks
	THINC Integrated Tool	At 8, 16 and 26 weeks
	EuroQol-five-Dimensions-five-Level	At 8, 16 and 26 weeks
	Work and Social Adjustment Scale	At 8, 16 and 26 weeks
	Patient Acceptability (1–5 scale)	After each TMS session and at 8, 16 and 26 weeks
	Adverse Events Checklist	After each TMS session and 8 weeks
	MRI scan (structural (T1), diffusion-weighted imaging (DWI) for structural connectivity, resting state fMRI for functional connectivity (FC) and effective FC (eFC), and GABA MRS of the DLPFC and insula	T1, DWI, FC, eFC at baseline (all centres) GABA at baseline and T1, DWI, FC, eFC, GABA at 16 weeks (all sites except London).

DLPFC, dorsolateral prefrontal cortex; fMRI, functional MRI; MRS, MR spectroscopy; TMS, transcranial magnetic stimulation.

We will explore moderators of depression response at 16 weeks, namely severity of depression by baseline HDRS-17 score, degree of treatment resistance, childhood trauma and age. The number of TMS sessions attended will be explored as a mediator of outcome in exploratory subgroup analyses of the depression response at 16 weeks.

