### Safety considerations

Internationally agreed definitions of adverse events (any untoward medical occurrence in a clinical trial subject administered TMS whether or not it has a causal relationship with TMS) and serious adverse events (any adverse event or adverse reaction that results in death, is life-threatening, requires hospitalisation or prolongation of existing hospitalisation, results in persistent or significant disability or incapacity, or is a congenital anomaly or birth defect). All participants will be asked about adverse events after every treatment (immediately and a maximum of 72 hours later) until they are resolved. Any participant found to be at risk to themselves (suicide, neglect) or others, or developing a serious adverse event will be referred to relevant clinical services. A review by a clinical expert in TRD will be offered to any participant whose depression has become more severe at 16 and 26 weeks for safety reasons.

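### The 26-week response, remission and sustained-response outcomes do not distinguish a lasting TMS effect from response after treatment added once the 16-week medication rule ends

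*Protocol article*

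**What the plan says.** All references are to the protocol article.

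- **Interventions** sets the medication rule: "Medication will be unchanged over 16 weeks follow-up unless there is clinical risk of harm". No rule is stated for weeks 16 to 26.
- **Study schedule** says of later treatment: "We will note any changes in medication or other forms of treatment".
- **Efficacy analysis and Table 3** define the 26-week binary outcomes on the HDRS-17. Response is a reduction of at least 50% from baseline and is listed as "Response (as defined above) at 8 weeks and at 26 weeks". Remission is a score of 7 or less. Sustained response is "defined as a continuing response as defined above following a response at the previous time point". In the analysis, "sustained responders at both 16 and 26 weeks will be compared between groups using logistic regression", adjusted for centre, baseline HDRS-17 and MGH score. None of these definitions mentions treatment added during follow-up.
- **Safety considerations** adds: "A review by a clinical expert in TRD will be offered to any participant whose depression has become more severe at 16 and 26 weeks".
- **Study schedule** fixes the primary outcome at the end of the stable-medication period: "The primary outcome measure is a binary variable of responder or non-responder at 16 weeks".

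**The concern.** Sustainability of response is among the things the trial sets out to explore (strengths and limitations list). The Introduction motivates cgiTBS by the short benefit of rTMS, and the Discussion frames the research need as sustained improvement. The 26-week outcomes carry that question.

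As defined, they are HDRS-17 snapshots. Two kinds of participant are counted in a way that does not reflect durability of TMS:

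- a week-16 non-responder who starts a new treatment, improves, and is a responder or remitter at week 26;
- a week-16 responder who relapses, is re-treated, recovers by week 26, and is scored as sustained.

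If such cases are common, the 26-week rates overstate how long the TMS effect lasts. An apparent fading or persistence of an arm difference then cannot be attributed to TMS from these outcomes alone.

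**Working it through.** **Inputs from the Sample size section.** Response of 26.5% (rTMS) and 41.5% (cgiTBS), two-sided 5%, 80% power, 15% loss, 184 per arm.

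**The plan's own figure.** With pooled variance, mean proportion 0.34 and no continuity correction:

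n = [1.960 × √(2 × 0.34 × 0.66) + 0.842 × √(0.265 × 0.735 + 0.415 × 0.585)]² / 0.15² = 155.4, so 156 per arm.

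156 / 0.85 = 183.5, so 184 per arm and 368 in total. This matches; power at 156 per arm is 80.2%. The sample size is not in dispute. It is used here only as a scale.

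**Assumed inputs.** The documents give no relapse or rescue rates, so these are illustrations:

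- p: response rate from TMS alone (26.5% and 41.5%);
- r: proportion of week-16 responders who relapse by week 26;
- g: probability that a non-responder or relapser is a responder at week 26 because of added treatment.

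**26-week response.** Observed rate = p + (1 − p) × g.

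| g, rTMS | g, cgiTBS | rTMS | cgiTBS | Difference (points) |
|---|---|---|---|---|
| 0 | 0 | 26.5% | 41.5% | 15.0 |
| 0.10 | 0.10 | 33.9% | 47.4% | 13.5 |
| 0.25 | 0.25 | 44.9% | 56.1% | 11.25 |
| 0.15 | 0.05 | 37.5% | 44.4% | 6.9 |
| 0.05 | 0.15 | 30.2% | 50.3% | 20.1 |

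With equal g the difference is 15 × (1 − g) points, so it shrinks. At 156 per arm, power for that comparison goes from 80% to 68% (g = 0.10) and 51% (g = 0.25). With unequal g the difference changes by 0.585 × g(cgiTBS) − 0.735 × g(rTMS). It therefore widens once g on cgiTBS exceeds g on rTMS by a factor of 0.735 / 0.585 = 1.26.

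**Sustained response at week 26.** A week-16 non-responder cannot qualify, so only relapse and recovery among week-16 responders matters. Observed rate = p × [1 − r × (1 − g)].

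| r, rTMS | r, cgiTBS | g (both arms) | rTMS | cgiTBS | Difference (points) |
|---|---|---|---|---|---|
| 0.30 | 0.30 | 0 | 18.6% | 29.1% | 10.5 |
| 0.30 | 0.30 | 0.25 | 20.5% | 32.2% | 11.6 |
| 0.50 | 0.20 | 0 | 13.3% | 33.2% | 19.95 |
| 0.50 | 0.20 | 0.25 | 16.6% | 35.3% | 18.7 |

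Added treatment raises each arm's rate by p × r × g. With the same g in both arms, the difference widens unless relapse on rTMS exceeds relapse on cgiTBS by a factor of more than 0.415 / 0.265 = 1.57.

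**Where the expert review acts.** Read as worse than baseline, a participant who is more severe at week 16 is a non-responder and already excluded from sustained response at week 26. The week-26 review follows the week-26 score and cannot change it. The week-16 review can therefore bear on 26-week response and remission, but hardly on sustained response. The reference point for worsening is not stated; if it meant worse than week 8, a current responder could be reviewed.

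**The case against.** **The HDRS-only comparison is legitimate.** Scoring everyone by randomised arm, whatever treatment follows, is a treatment-policy comparison. Referring teams are blinded, so later prescribing should not follow knowledge of allocation. This stands, and it is why that comparison should remain the main result. An analysis that counts added treatment as failure answers a second question. It also misclassifies participants whose treatment changed for reasons unrelated to relapse.

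**The detail may sit elsewhere.** Handling of treatment changes is often left to the full protocol or SAP, neither of which is shown. This limits the point but does not remove it: the article states the outcome definitions, and as stated they count re-treated relapse as sustained response.

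**Treatment data are not wholly unused.** Medication and service use enter the economic evaluation. That is correct; the gap is confined to the efficacy outcomes.

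**Stronger readings that the documents do not support.**

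- A reader might infer that added treatment necessarily shrinks the arm difference. The calculations show either direction, and the documents give no rates to decide it.
- A reader might take the expert review as a route to rescue that inflates sustained response. The text offers a review on safety grounds and does not say that treatment follows, and the review hardly reaches that outcome.
- A reader might extend the problem to the primary result. Changes after week 16 cannot alter a week-16 outcome.

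**Conclusion.** The point holds as a limited one about secondary outcomes. Medication is fixed only to week 16, changes are recorded, and the 26-week binary outcomes ignore them. Response after treatment added between weeks 16 and 26 is therefore indistinguishable from lasting TMS response. Absolute 26-week rates can be inflated in both arms, and the arm difference can move either way.

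The size cannot be fixed from the documents. In the illustrations, rescue acting equally in both arms reduces a 15-point difference in 26-week response to 13.5 or 11.25 points, and unequal rescue gives 6.9 to 20.1. The sustained-response difference moves by little more than one point, up or down. These values rest on the plan's response rates, on assumed relapse and rescue rates, and on added treatment never making a participant worse. This is a cheap improvement in what the trial can say about durability, not a correction of an invalid analysis.

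**What to change.** 1. Keep the HDRS-only comparison by randomised arm as the main result for 26-week response, remission and sustained response, and state that it is a treatment-policy comparison.
2. Add one prespecified supplementary analysis of these three outcomes. Participants with a recorded new or increased antidepressant treatment (including ECT or further TMS) between week 16 and week 26 are scored as not having the outcome. Use the same adjusted logistic regression.
3. Report these treatment changes by arm.
4. Interpret any statement about durability of the TMS effect in the light of both results.

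Clinical care is unchanged. The cost is a paragraph of analysis text and the coding of data already recorded. The downside is one extra result per 26-week binary outcome, with lower absolute rates, and some treatment changes unrelated to relapse counted as failures.
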